##### iMTA Medical Consumption Questionnaire

The iMTA Medical Consumption Questionnaire (iMCQ) is a generic, nondisease-specific instrument for measuring (direct) medical costs [52]. The instrument is a standardized self-reported questionnaire. The iMCQ includes questions related to frequently occurring contacts with health care providers and can be complemented with extra questions that are relevant for specific study populations. A manual is available for a structured use of the questionnaire. For the valuation of resource use, as obtained from the iMCQ, reference unit prices can be used. These reference prices can be derived from the Dutch manual for costing studies. The manual was commissioned and published by Zorginstituut Nederland and authored by the Institute for Medical Technology Assessment (iMTA) [53].

#### MRI Abdomen After Splenic Artery Embolization

Patients in the retrospective study will undergo MRI once at the ETZ Hospital in Tilburg, and patients in the prospective study will undergo MRI 1 month and 1 year after treatment at the hospital where the treatment took place. Not all hospitals have the same MRI scanner. However, the same scan protocol will be used at all locations, leading to comparable images and assessments (see Table 4).

Only patients treated with SAE will receive an MRI of the upper abdomen to evaluate the spleen morphologically (volume, necrosis, splenosis, calcifications, and chronic infarction) and dynamically (diffusion and enhancement).

**Table 4 table4:** Magnetic resonance imaging scan protocol.

Retrospective study	Prospective study
Axial Dual FFE^a^/GRE^b^ (in-out phase); Coronal T2-weighted TSE^c^/FSE^d^; Axial T2-weighted TSE/FSE; Axial BFFE^e^/BGRE^f^ Volume (5 mm slices, no gap); Axial DWI^g^ with b value=0/400/800	Axial Dual FFE/GRE (in-out phase); Coronal T2-weighted TSE/FSE; Axial T2-weighted TSE/FSE; Axial BFFE/BGRE Volume (5 mm slices, no gap); Axial DWI with b value=0/400/800
3D^h^ (noncontrast)	Axial dynamic T1-weighted noncontrast with fat sat; Axial T1-weighted 3D magnetic resonance angiography contrast-enhanced; Axial dynamic T1-weighted contrast-enhanced (2 time points) with fat sat

^a^FFE: Fast Field Echo.

^a^GRE: Gradient Echo.

^c^TSE: Turbo Spin Echo.

^d^FSE: Fast Spin Echo.

^e^BFFE: Balanced Fast Field Echo.

^f^BGRE: Balanced Gradient Echo.

^g^DWI: Diffusion Weighted Images.

^h^3D: three-dimensional.

### Statistical Analysis

All analyses will be conducted using SPSS V24.0 (Statistical Package for Social Sciences, Chicago Illinois, USA). Frequencies and descriptive statistics will be calculated to provide an overview of the characteristics of the study population. Statistical test results will be considered significant at a level of *P*<.05.

Concerning the retrospective study, a MANCOVA will be done after correcting theoretically important covariates to assess the differences between treatment groups on the 4 WHOQOL-Bref domains and the general facet. For each type of treatment, a 1 sample *t* test will be performed for each WHOQOL-Bref scale to compare the QOL scores with reference data.

For both the retrospective and prospective studies, a logistic regression analysis will be performed on the outcome variables’ (1) need for reintervention (yes/no) and (2) for each complication (yes/no), assessing the effect of treatment after correcting for theoretically important covariates. With regard to hospital stay in days, a Kruskal-Wallis test will be performed with the group (type of treatment) and days in hospital. Analysis of covariance will be used to compare proximal versus distal SAE, thereby correcting the effect for theoretically important covariates. To confirm/find prognostic factors for failure of NOM, a logistic regression analysis will be performed if NOM is a failure quickly after treatment. Otherwise, a survival analysis will be performed.

Regarding the prospective study, to assess the differences between groups in their change in QOL over time, a linear mixed model analysis will be conducted. To answer our research question, we will focus on the interaction effect between measurement occasion and treatment group, while correcting for theoretically important covariates. For the repeated measures, an unstructured covariance matrix will be used. Item-level missing values will be imputed according to the guidelines of the questionnaires. Scale-level missing values will be handled directly through maximum likelihood estimation, because the mixed model procedure makes use of all available data for each participant over all time points.

To conduct the cost-effectiveness analysis, a cost-effectiveness model will be developed. This model will comprise 2 treatment arms; SAE will be compared with splenectomy. The cost-effectiveness study will be conducted according to the most recent Dutch guidelines for health economic research [54]. As such, the study will be performed from the societal perspective, which means that all costs and benefits should be considered, regardless of by whom the costs are borne or to whom the benefits accrue.

Effects will be expressed in quality-adjusted life years, which constitute a combination of QOL and length of life. QOL will be measured in utilities. Utilities express QOL on a scale from 0 (death) to 1 (perfect health). Utilities can be derived from the EQ-5D-5L [44]. Survival will be derived from international clinical literature. Costs will be estimated according to the Dutch Manual for Costing in Economic Evaluations, update 2015, using a societal perspective [54]. A bottom-up methodology will be used to compute costs; the total number of medical contacts will be multiplied with unit costs. Direct medical costs comprise all costs directly relating to the prevention, diagnostics, therapy, rehabilitation, and care of the intervention. Health care utilization will be derived from the iMCQ [52]. The iPCQ will be used to assess productivity losses [51]. The friction cost method will be used for the calculation of costs because of production losses [55]. This method is the expertise of the iMTA; it is its standard method and has been widely used.

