### Study Procedures

#### Retrospective Study

The clinical and imaging data of all splenic injury patients will be collected from the electronic patient files and registered anonymously. To measure QOL, all patients who are still alive will receive a written letter explaining the study, an informed consent form, the questionnaires, and a prestamped return envelope by mail. When a patient is willing to participate, he/she will sign the consent form and send it back in the return envelope, together with the completed questionnaires, assessing QOL and health status. When patients do not complete or return the questionnaires within 2 weeks, they receive a phone call as a reminder. When patients do not want to participate, the reason will be noted if the patient wants to let it be known. The patients who underwent SAE will be called for a voluntary single MRI abdomen at the ETZ Hospital in Tilburg.

This study has been reviewed and approved by the Medical Ethical Committee Brabant (METC Brabant, protocol number: NL54339.028.15) on January 27, 2016. The study has also been approved by the local ethical committee of the ETZ Hospital on February 9, 2016.

**Table 1 table1:** Minimal clinically important difference (MCID) per WHOQOL-Bref domain.

Domain	MCID	SD	Cohen *d*	Cohen *f*	Effect size *f*^2^
Physical	1.545	3.1	0.498	0.249	0.062
Psychological	1.259	2.5	0.504	0.252	0.063
Social	1.274	2.6	0.490	0.245	0.060
Environmental	1.142	2.3	0.497	0.248	0.062
General	0.876	1.8	0.487	0.243	0.059
Average	1.219	2.460	0.495	0.248	0.061

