#### Prospective Study

In each participating hospital, an interventional radiologist and a trauma surgeon will be designated as principal investigators. Each hospital will also have a research assistant, most likely a radiology technologist or a member of the research team. The daily work will be carried out by the research assistant under the supervision of the principal investigator at the ETZ Hospital (CR). The research assistant will check daily whether potential eligible patients were admitted to the hospital. This will be done by checking the subscription list, verbally checking with the attending (resident) radiologist and trauma surgeon, and verifying the data in the electronic patient record. The subscription list will be placed at the dictation station of the radiologist, where the trauma diagnoses are reported. If a patient is treated for a traumatic spleen injury, baseline characteristics will be collected and he/she will be screened for the inclusion and exclusion criteria. The clinical data of all eligible patients will be collected anonymously in the database. As soon as the patient can talk and is lucid, the assistant will visit the patient to provide a verbal and written explanation about the study. The time for consideration of participation is 1 week. When a patient is willing to participate, he/she will sign a consent form. If not, the reason will be noted if the patient wants to let it be known. Each inclusion will be reported to the principal investigator (CR). Total follow-up time is 1 year after treatment with time points at 1 week and 1, 3, 6, and 12 months after treatment.

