#### Clinical Data

For both the retrospective and prospective study, data will be collected from the electronic patient records and trauma registry (Network Emergency Care Brabant). The trauma registry compiles prehospital and hospital data of all trauma patients admitted after presentation to the emergency department. Patients with splenic injury will be identified by the International Statistical Classification of Disease and Related Health Problems (ICD-10) and Abbreviated Injury Scale (AIS) diagnosis codes starting with S36.x and 5442, respectively.

The collected data concern the following: age, sex, systolic blood pressure, hemoglobin, Glasgow coma scale (at arrival), intubation (Yes/No), imaging (US and/or CT), grading spleen injury (American Association for the Surgery of Trauma; see Table 2)[28], type of treatment (NOM/SAE/splenectomy), complications, hospital stay (days), spleen in situ at discharge (Y/N), reinterventions (Y/N), rehospitalization (Y/N), and mortality.

**Table 2 table2:** American Association for the Surgery of Trauma spleen injury scaling (1994 Revision).

Grade^a^		Injury description
**I**		
	Hematoma	Subcapsular <10% of surface area
	Laceration	Capsular tear <1 cm parenchymal depth
**II**		
	Hematoma	Subcapsular 10%-50% of surface area; or intraparenchymal <5 cm in diameter
	Laceration	1-3 cm parenchymal depth, which does not involve a trabecular vessel

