Several factors related to the design and execution must be taken into account. First, patients will be treated with NOM, SAE, or surgery for a specific clinical condition. It may be the clinical situation that determines the long-term outcome, although that outcome is not or partially the result of the treatment. This risk is confounding by indication: the risk that the groups are in fact not easily comparable (ie, selection bias). To keep this to a minimum, the reason for choosing a particular treatment will be registered. In our analysis, we will correct for these confounding factors using propensity score analysis. Correction is only possible when adequate and good-quality information is available about the clinical condition of the patients, which led to the decision. The patient’s record will be searched thoroughly to find this information. Second, trauma patients often have multiple injuries that can affect QOL and clinical outcomes. We are not primarily interested in these additional injuries, but these will be included as a covariate in the analysis. Third, response bias may occur in the questionnaires group. Patients may decline participation because they are not interested or it may be too confronting to think/correspond about their psychological state. Fourth, the severely injured patients may be overrepresented in the nonresponse group concerning the questionnaires. To limit this, these patients will be visited as soon as they are approachable and, if necessary, will be provided assistance to complete the questionnaires. Fifth, the absence of randomization is a (strong) limitation and a potential source of bias, but randomized comparison in managing trauma patients is virtually impossible. Furthermore, it will have strong ethical implications as it is well known that randomizing trauma patients with intraabdominal bleeding, potentially unstable, is something not feasible in clinical practice. Sixth, the sample size calculation is based on the primary objective of the study. For the clinical and cost-effectiveness analysis, this implies that because of the small sample size, the uncertainty about the outcome is large. Seventh, we are aware of response shift bias. Response shift is a change in self-reported QOL that is a result of a change in internal standards (ie, recalibration), values (ie, reprioritization), or meaning of QOL (ie, reconceptualization) [56,57]. Thus, response shift reflects psychological adaptation: we do not consider this as a problem but as a fact of life. In addition, the method to prevent response shift contains recall bias itself. Considering this, and the fact that QOL is a generic outcome measure, ensures that we use the chosen method. Moreover, the retrospective patients will not be included in the prospective study.

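### The retrospective comparison of QOL with reference data uses questionnaire responders only, without adjustment, although the protocol warns of severity-related non-response

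*Protocol article*

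**What the plan says.** The primary objective is QOL after treatment for splenic injury, so the level of QOL in each treatment group matters as well as the contrast between groups.

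- **Comparison of level.** Under Statistical Analysis, the retrospective study has a one-sample t test for each treatment, which "will be performed for each WHOQOL-Bref scale to compare the QOL scores with reference data". No covariate or weight is mentioned.
- **Comparison between treatments.** Adjustment is stated here: "a MANCOVA will be done after correcting theoretically important covariates to assess the differences between treatment groups". The Discussion adds a propensity score for choice of treatment and additional injuries as a covariate.
- **How retrospective QOL is obtained.** Under Study Procedures, surviving patients are sent the questionnaires once, by mail. Those who do not reply within 2 weeks are telephoned.
- **Acknowledged risk.** The Discussion says "response bias may occur in the questionnaires group" and that "the severely injured patients may be overrepresented in the nonresponse group concerning the questionnaires". The remedy attached to the second risk is that "these patients will be visited as soon as they are approachable and, if necessary, will be provided assistance to complete the questionnaires".
- **Data on non-responders.** For the retrospective study, "The clinical and imaging data of all splenic injury patients will be collected from the electronic patient files and registered anonymously". The Clinical Data section lists, among others, "age, sex, systolic blood pressure, hemoglobin, Glasgow coma scale (at arrival), intubation (Yes/No), imaging (US and/or CT), grading spleen injury", as well as treatment, complications and hospital stay.

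**The concern.** The one-sample t test estimates the mean QOL of those who replied. The question is the mean QOL of those who were treated. The two differ if the chance of replying depends on something that also affects QOL, and the protocol itself names injury severity as a candidate.

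No stated tool deals with this for the retrospective reference comparison. Bedside help suits patients still in care, not people written to up to about 12 years after injury (admissions January 2005 to February 2017, screening February 2017). The propensity score concerns which treatment was given, not who replied. The MANCOVA covariates serve the contrast between treatments. Maximum likelihood is described for the prospective mixed model, and retrospective non-responders have no QOL measurement for it to use.

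At stake is a real deficit against the reference population that looks smaller than it is, or is missed, by an amount that varies with the case mix of each treatment group.

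**Working it through.** **Figures from the protocol.** Table 1 gives an MCID of 1.545 and an SD of 3.1 for the physical domain, so one MCID is 1.545/3.1 = 0.498 SD. The averages over scales are 1.219 and 2.460. The retrospective sample size of 138 is reproduced: MANOVA global effect, 3 groups, 5 outcomes, f² = 0.061, noncentrality 2 × 138 × 0.061, df 10 and 2 × (138 − 6) = 264, power 0.801. It is used below only to fix a group size.

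**Assumptions (not in the documents).** Let p be the share of severe patients in a treatment group, r_s and r_o the response probabilities of severe and other patients, and D the QOL gap between them. I take r_o = 0.70, r_s = 0.40 to 0.55, p = 0.60, and D from one MCID to one SD.

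**Formula.** The severe share among responders is p·r_s / [p·r_s + (1 − p)·r_o]. The bias is D × (p − that share).

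**Size at p = 0.60, physical domain.**
- r_s = 0.40: share 0.24/(0.24 + 0.28) = 0.4615, so bias = 0.1385 × D. With D = 1 SD this is 0.1385 × 3.1 = 0.43 points, 28% of the MCID. With D = 1 MCID it is 14%.
- r_s = 0.55: share 0.33/(0.33 + 0.28) = 0.541, so bias = 0.059 × D. With D = 1 SD this is 0.18 points, 12% of the MCID. With D = 1 MCID it is 6%.

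**Dependence on severity mix (r_s = 0.40, r_o = 0.70, D = 1 SD).**

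| Severe share p | Severe share among responders | Bias (SD) |
|---|---|---|
| 0.20 | 0.08/0.64 = 0.125 | 0.075 |
| 0.40 | 0.16/0.58 = 0.276 | 0.124 |
| 0.60 | 0.24/0.52 = 0.462 | 0.138 |
| 0.80 | 0.32/0.46 = 0.696 | 0.104 |
| 0.90 | 0.36/0.43 = 0.837 | 0.063 |

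The bias rises and then falls, with its peak at about 57% severe here.

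**Effect on the unadjusted gap between two treatments.** At 60% versus 20% severe, the true gap of 0.40 SD becomes 0.462 − 0.125 = 0.34 SD among responders. At 80% versus 40%, the true gap is again 0.40 SD but becomes 0.696 − 0.276 = 0.42 SD. The direction depends on the mix.

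**Effect on the t test.** Take 138/3 = 46 responders per treatment (equal groups assumed), SD 2.46 and a true deficit of 1.219. Power is 0.91 without bias, 0.81 with bias 0.17 (0.1385 × 1.219) and 0.66 with bias 0.34 (0.1385 × 2.46). With 30 responders the three values are 0.75, 0.62 and 0.47.

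**The case against.** The strongest objection is that nothing in the article is contradicted: it lists non-response openly as a limitation, and sensitivity analyses for non-response are often left to a full protocol or SAP, neither of which is shown. That would dispose of a complaint about missing detail. Here, however, the article fixes a specific test and a specific remedy, and for the mailed cohort the remedy does not fit. A full protocol or SAP may still contain the missing step.

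Other objections stand and limit the point:

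- The Discussion says severe patients may be overrepresented among non-responders. It does not say that this is expected.
- Visits are not the only effort made. Retrospective non-responders are telephoned, and reasons for refusal are noted where given. Neither adjusts the estimate.
- The direction is not certain. The Discussion also mentions lack of interest, which could include well-recovered patients, and distress, which recorded injury severity may not capture.
- Every response rate and severity share above is assumed. A one-SD gap persisting for years is about twice the MCID and sits at the high end.

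A reader might go further in three ways that the documents do not support:

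1. *QOL is overstated most in the most severely injured treatment group.* The table shows less bias at 80% severe than at 40%. The statement would need a wider response gap or QOL gap in that group.
2. *The contrast between treatments shrinks, so the MANCOVA and mixed model need weighting too.* The unadjusted gap can widen as well as shrink. The planned contrasts are adjusted for covariates, and the Discussion adds a propensity score. If response depends on measured severity, conditioning on it largely removes this selection from the contrast.
3. *Anonymous registration would prevent the linkage.* The prospective section uses similar wording, "The clinical data of all eligible patients will be collected anonymously in the database". But reminder calls require knowing who has replied, and a covariate-adjusted MANCOVA requires questionnaires to be linked to clinical data. Responder status should therefore be recoverable, and the worry is speculative.

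**Conclusion.** The point holds for the retrospective comparison with reference data. That analysis uses responders only, is unadjusted, and is exposed to a selection that the protocol itself raises and does not address for this cohort.

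If severe patients respond less and still have lower QOL at the time of the questionnaire, QOL is overstated, by an amount that differs between treatments. At 60% severe and the assumed response rates and QOL gaps, the overstatement is about 6-28% of the MCID. It is unlikely to overturn a large deficit, but it is enough to weaken detection of a deficit of about one MCID. The ranking of bias across treatments cannot be stated from the documents.

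**What to change.** 1. Among surviving patients who were sent a questionnaire, tabulate responders against non-responders by treatment on the clinical data already collected.
2. Fit a parsimonious model for the probability of response, for example on treatment, AAST grade, age, Glasgow coma scale and hospital stay.
3. Report each comparison with reference data twice: unweighted as planned, and weighted by the stabilised, truncated inverse probability of response, with a standard error that allows for the weights.
4. State that the weighted result corrects only for measured factors, and qualify the reference comparison if the two versions differ materially.

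The cost is analysis time. The Results section says that retrospective data collection is complete, and no new patients or procedures are needed. Confidence intervals will be somewhat wider. With about 138 responders over three treatments, a response model with many predictors could give unstable weights, hence the short list. The between-treatment MANCOVA and the prospective mixed model need no change on this account.

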In blunt abdominal trauma, where the spleen is one of the most frequently injured organs, much is known about morbidity and mortality [12]. Internal bleeding caused by abdominal organ injury is one of the main causes of death after trauma, and a missed splenic rupture is the most common cause of preventable death in trauma patients [13,14]. Presently, the standard of care in hemodynamically stable patients is nonoperative management (NOM), involving close observation of the patient, with success rates up to 90% [12]. A recent study among adults with blunt splenic injury suggests that there are prognostic factors for failure of NOM. Strong evidence exists for prognostic patient factors such as age of 40 years or above, Injury Severity Score of at least 25, and American Association for the Surgery of Trauma splenic injury grade of 3 or higher [15]. Failure of therapy leads to more interventions, longer hospital stay, and higher mortality rates, resulting in increased costs and presumably decreased QOL. When NOM fails, angiography and splenic artery embolization (SAE) can be used as a supplement to NOM. The success rate of SAE ranges between 73% and 100%, with an overall success rate of NOM combined with SAE ranging between 86% and 100% (most studies reporting success rates greater than 90%) [16]. Despite this success rate, much remains unknown about splenic function after SAE, although it is speculated that there is a relationship between splenic volume and the immunologic status of the patient [17-20]. Preservation of splenic function might be one of the biggest advantages of NOM and SAE. However, patients treated with SAE have a risk of developing splenic infarction, abscesses, or cysts, with distal embolization having a significantly higher association with major complications compared with proximal embolization [21,22]. Surgery is indicated when a patient is hemodynamically unstable and does not respond to transfusion or when associated intraabdominal injuries require surgical management. Possible disadvantages of surgery are postsplenectomy complications, such as sepsis, thrombocytosis, and a lifetime risk of invasive infections (overwhelming postsplenectomy infection) [23,24]. All complications may have a major impact on patients’ QOL.

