### Participants and Centers of Recruitment

#### Retrospective Study

The study population comprises patients who had a splenic injury after blunt abdominal trauma and were admitted for treatment in the ETZ Hospital (Elisabeth-TweeSteden Ziekenhuis) in Tilburg, the Netherlands, between January 2005 and February 2017. It concerns both men and women who were 18 years or older at the time of screening (February 2017).

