### Inclusion and Exclusion Criteria

#### Retrospective Study

The inclusion criteria are patients (1) diagnosed with splenic injury after trauma; (2) who underwent NOM, SAE, or surgery at the ETZ Hospital; (3) diagnosed between January 2005 and February 2017; and (4) who were aged 18 years or older at the time of screening (February 2017). Patients will be excluded from questionnaires in case of (1) insufficient knowledge of the Dutch language (verbal and writing) or (2) obviously, death. Patients treated with SAE will be excluded for magnetic resonance imaging (MRI) when they do not want to or are not able to undergo an MRI abdomen (eg, pregnancy or other contraindications).

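### Retrospective complications and reinterventions are analysed as yes/no with no common observation window, although admissions span about 12 years and at least one named complication can occur late

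*Protocol article*

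**What the plan says.** The Statistical Analysis section prescribes one method for two outcomes, need for reintervention and each complication, both coded yes/no: "For both the retrospective and prospective studies, a logistic regression analysis will be performed on the outcome variables". The treatment effect is to be adjusted for covariates that are not named. The same paragraph makes the method depend on timing for one other outcome only: failure of nonoperative management gets logistic regression if it comes quickly, and survival analysis otherwise.

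The two cohorts are observed differently. In the prospective cohort, "Total follow-up time is 1 year after treatment". Retrospective patients were admitted "between January 2005 and February 2017". Their data source is given under Study Procedures: "The clinical and imaging data of all splenic injury patients will be collected from the electronic patient files and registered anonymously". No date is given to which the files are read. The Clinical Data section lists "complications, hospital stay (days), spleen in situ at discharge (Y/N), reinterventions (Y/N), rehospitalization (Y/N), and mortality". In that list only the presence of the spleen is tied to discharge, and no event date or observation time appears.

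Among the possible disadvantages of surgery, the Background section names "a lifetime risk of invasive infections (overwhelming postsplenectomy infection").

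**The concern.** A yes/no outcome is a risk over some period, and logistic regression compares treatments fairly only if that period is the same for everyone or is unrelated to treatment. In the retrospective cohort the period is not defined. If events are counted for as long as each file runs, a patient admitted in 2005 has had up to 12 years longer to record a late event than one admitted in early 2017, yet both enter the model as a plain yes or no.

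This matters for outcomes that can occur late, of which post-splenectomy infection is the clear example in the article. Should one treatment have been used more in the earlier years, its odds ratio for late events would rise through exposure time alone. Clinical outcome and its relation to quality of life is a stated secondary objective, and the results may feed a management protocol.

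**Working it through.** **The plan's own figure.** The article gives no figure for this analysis. Its only retrospective sample size, 138, belongs to the quality-of-life MANCOVA. It reproduces (3 groups, 5 scales, *f*² = 0.061, alpha .05: N = 138, power 0.801) and is not affected.

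**Inputs from the article**
- Admission span: 31 January 2005 to 1 February 2017 is 12.0 years; 1 January 2005 to 28 February 2017 is 12.2 years. I use 12.1.
- Prospective follow-up: 1 year.

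**Inputs assumed, because the article gives none**
- Late-event hazard *h* = 0.01 per year, the same in both treatments, so that any odds ratio other than 1 is artefact.
- Mean follow-up *t*₁ and *t*₂ in two treatments.
- Early-event share *e* = 0 or 0.10.

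**Formulas.** Late risk: *P*(*t*) = 1 − exp(−*ht*). With early events: *P\** = *e* + (1 − *e*)*P*. Odds ratio = [*P*₁/(1 − *P*₁)] / [*P*₂/(1 − *P*₂)].

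| Mean follow-up (years) | Risks, all events late | OR | Risks, 10% early | OR |
|---|---|---|---|---|
| Equal | equal | 1.00 | equal | 1.00 |
| 7 v 5 | 6.8% v 4.9% | 1.41 | 16.1% v 14.4% | 1.14 |
| 9 v 4 | 8.6% v 3.9% | 2.31 | 17.7% v 13.5% | 1.38 |

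For example, 9 v 4 with all events late: (0.0861/0.9139) / (0.0392/0.9608) = 0.0942/0.0408 = 2.31.

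**How large a calendar shift these gaps imply.** Suppose files are read to February 2017 and admissions are spread evenly. Patients from the first half of the window then average ¾ × 12.1 = 9.1 years and those from the second half ¼ × 12.1 = 3.0 years.
- Complete separation of two treatments into the two halves gives a gap of about 6.05 years, so 9 v 4 is a strong shift (5/6.05 = 83% of that).
- A 70/30 split gives 0.7 × 9.075 + 0.3 × 3.025 = 7.3 years against 0.3 × 9.075 + 0.7 × 3.025 = 4.8 years, which is close to 7 v 5.

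Averaging the risk over follow-up spread evenly within each half, for *h* from 0.005 to 0.05 per year:

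| Shift | OR, all events late | OR, 10% early |
|---|---|---|
| None | 1.00 | 1.00 |
| 70/30 | 1.51 to 1.62 | 1.10 to 1.45 |
| Complete | 3.05 to 3.58 | 1.27 to 2.58 |

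**If files are read to a later date.** Every patient gains the same time, so the spread stays at about 12 years but the ratio shrinks. With 2 further years (assumed), 7 v 5 becomes 9 v 7, OR (e^0.09 − 1)/(e^0.07 − 1) = 0.0942/0.0725 = 1.30. Likewise 9 v 4 becomes 11 v 6, OR 0.1163/0.0618 = 1.88.

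**With a common 1-year window.** Both risks are 1 − exp(−0.01) = 1.0%, and the odds ratio is 1.00 whatever the calendar mix.

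**The case against.** The strongest case against rests on four points.

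1. *The exposure time is inferred.* The eligibility text "who were 18 years or older at the time of screening (February 2017") uses February 2017 for age, and the same month closes admissions; it is not a date at which records stop. Nor does the article say that events are counted to the end of each file. Complications and reinterventions stand in a list made up largely of admission items. If the events are mostly early, logistic regression is suitable. This stands, and it limits the concern to late events. It does not supply the missing window.

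2. *The bias needs a shift in treatment mix.* A reader might infer that treatments used earlier will simply collect more events. The article reports no change in treatment use over the years, and without one the spurious odds ratio is 1.00. This stands in full, so the bias is conditional.

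3. *An article leaves such detail to the full protocol.* Time since injury could be among the unnamed covariates, and the Discussion adds a propensity score. That score, however, is aimed at the reasons for treatment choice. Also, the method itself is stated here, and the same paragraph lets timing decide the method for failure of nonoperative management but not for these outcomes. The point therefore concerns a stated method and not only an omitted detail.

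4. *Equal hazards are unrealistic for a complication tied to one treatment.* True, but the assumption serves only to isolate the artefact; it is not a forecast.

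Two further inferences are not supported. Rehospitalization is collected, but no logistic model for it is planned. And the article nowhere claims that the 1-year prospective data show lifetime infection risk, so no disclaimer is needed. Abscesses and cysts after embolization are named without any timing, so only post-splenectomy infection can be called late on the article's own words.

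**Conclusion.** The concern holds in a conditional form. The article fixes ever/never logistic regression for reintervention and each complication in a cohort admitted over about 12 years, with no common window and no allowance for observation time. Whether this tilts the treatment comparison depends on three things that the article does not give: how far forward the files are read, what share of events is late, and whether treatment use changed between 2005 and 2017.

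At an assumed 1% per year in both treatments, the artefact is an odds ratio of about 1.4 for a gap of 7 v 5 years, about 2.3 for 9 v 4, and 1.0 for no gap. With 10% early events the first two fall to about 1.1 and 1.4. These are illustrations, not estimates of the bias in this study. The objective is secondary, and the Discussion already warns of large uncertainty in the clinical analysis. The weakness is nevertheless cheap to remove and worth removing.

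**What to change.** In the Statistical Analysis section:

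- Define reintervention and each complication as occurring within 1 year of treatment in both cohorts. This matches the prospective follow-up.
- Keep logistic regression for patients whose records cover the full year. If some have less, use a time-to-event model for this outcome, since a binary logistic model cannot handle censoring. Patients who die within the year without the event fall under the same rule; they should be neither dropped nor counted silently as a no.
- Analyse later events in the retrospective cohort by time to event, with a stated common record cut-off date and with death either as a competing event or as censoring, whichever is chosen being stated.
- Tabulate treatment by admission year, so that readers can see whether a shift exists at all.

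Cost: a few lines of analysis wording, and event dates to be read from the files. The database is reported as complete, and the listed items include no event dates, so this may mean returning to the files. The drawback is that late events leave the main yes/no analysis and move to a separate, imprecise one.
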